### Participants

Participants will be recruited from a physiotherapy outpatient clinic at a large public hospital and two private physiotherapy clinics, all within metropolitan Melbourne, using internal flyers and social media to promote participation. Since SPS is seen in both general and sporting populations, a combination of public and private sector recruitment sites will ensure a broader pool from which to draw participants. Based on a previous study [15] investigating the use of exercise in SPS with an effect size of 0.66 and maintaining a power of 0.80, calculations indicate a minimum of 30 patients would be required in each group for a full-scale RCT. To determine the feasibility for a full-scale RCT, a sample of 36 across the three groups (12 per group) has been chosen for this pilot study. This is approximately 30% of the calculation for a full-scale RCT [39] with an allowance for drop outs. It is anticipated that this sample size will provide the opportunity to observe recruitment rates using the assessment algorithm, adherence to and compliance with the various components of the intervention, number of participants lost to follow-up and number of adverse events; as well as enable preliminary evaluation of clinical outcome trends while saving the costs associated with a full-scale trial.

**Fig. 1 Fig1:**
[figure not shown]
Study flow. *SPS* subacromial pain syndrome, *WORC* Western Ontario Rotator Cuff Index, *SPADI* Shoulder Pain and Disability Index, *NRS* numerical rating scale, *GRCS* global rating of change score

### Eligibility

There is no definitive diagnostic tool for SPS with no single impingement test shown to have high specificity or sensitivity [40, 41]. Further, a lack of consensus has been highlighted in the literature regarding participant eligibility criteria used in studies investigating this disorder [42]. Based on best available evidence [40, 41, 43–45], the combination of patient history and an assessment algorithm designed specifically for this pilot study will be used to assess eligibility. The assessment algorithm is outlined in Fig. 2 and is based on the following inclusion/exclusion criteria.

**Fig. 2 Fig2:**
[figure not shown]
Assessment algorithm

### Inclusion criteria

These include (i) aged 18–80 years (likelihood of patients > 80 having degenerative changes in the shoulder is increased), (ii) pain localised to the proximal anterolateral shoulder region, (iii) positive for pain on at least one of the following three impingement tests: Hawkins-Kennedy, Neer’s, Jobe’s and (iv) positive for pain on at least one of the following four tests: painful arc, drop arm test, lift-off test, and resisted external rotation.

### Exclusion criteria

These include (i) large, full-thickness rotator cuff tear, (ii) moderate-severe glenohumeral or acromioclavicular joint osteoarthritis, (iii) glenohumeral joint instability including previous shoulder dislocation/subluxation, (iv) previous shoulder fracture, (v) current neck pain/dysfunction with a somatic or radicular referral pattern indicative of cervical spine rather than shoulder as primary source of symptoms and/or pathology, (vi) neurological deficits of the upper limb and (vii) systemic inflammatory arthritic conditions.

Though patients routinely present with radiology including X-ray and ultrasound, which will be used to assist in diagnosis, inclusion/exclusion will be primarily based on clinical decision-making. Hence, where the patient meets the inclusion criteria outlined above, there must also be an absence of (i) positive rotator cuff lag signs (suggestive of a large rotator cuff tear), (ii) a passive external rotation range of motion deficit > 30° (suggestive of glenohumeral joint osteoarthritis) and (iii) a positive Spurling’s test (suggestive of cervical radicular/referred pain). To determine the severity of osteoarthritis, a shoulder X-ray undertaken within the previous 12 months is required for inclusion in the study.

### Procedures

Patients are referred to the public hospital physiotherapy outpatient clinic by their general practitioner or orthopaedic/other specialist. Those referred to the two private clinics may be referred by their general practitioner, orthopaedic specialist or via self-referral. Potentially eligible patients will be given information about the study. If they are interested in participating, their details will be passed to the study coordinator (RK) who will contact them to undertake a telephone screening interview. If still potentially eligible, the patient information and consent form will be mailed out and an appointment made for the patient to attend the clinic for further screening. Eligibility will be confirmed through a clinical assessment (using the assessment algorithm shown in Fig. 2) undertaken by a blinded assessing physiotherapist at each site.

Since there is a possibility of baseline differences in demographics between participants recruited from the public and private sectors, block randomisation will be used to ensure that participants from each of the clinics have an equal chance of receiving any of the interventions. Once consented, participants will be randomly allocated using an off-site randomiser and computer-generated allocation sequence to one of the three exercise groups: (i) isometric, (ii) isotonic concentric or (iii) isotonic eccentric. The treating clinician will be informed by the off-site randomiser via telephone of the group each participant is randomised to just prior to the commencement of the treatment intervention. While the treating physiotherapist cannot be blinded to treatment allocation, in order to minimise bias, the assessing physiotherapist will be blinded to group allocation, and patients will not be told which intervention group they have been randomised to.

The intervention will be carried out by designated, experienced physiotherapists at each site, with the treatment sessions delivered by a physiotherapist who is not involved in any stage of the assessment process. Prior to recruitment of participants into the study, all clinicians involved in assessment and treatment delivery will receive training in the assessment algorithm and treatment intervention along with all related procedures including treatment notes and documentation as per the study protocol. Treatment interventions including individual patient modifications will be recorded on standardised report forms. Participants will be provided with a logbook to record the number of home exercise sessions completed as well as adherence to the home exercise program. Adverse events and the use of co-interventions will also be recorded in the participant logbook. All adverse events will be documented by the treating physiotherapist and the project coordinator informed (RK). Monthly research staff meetings will be instigated for monitoring trial progress and to ensure prompt management of any issues that arise.

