### Outcome measures

#### Primary outcome: feasibility of a full-scale RCT

The primary outcome of this study is to determine feasibility for a full-scale RCT. This will involve an evaluation of (a) ease of recruitment (rate and number as well as suitability of the assessment algorithm), (b) adherence to both phases of the exercise intervention including home program compliance and logbook completion, (c) participant non-completion (drop out number and rate) and (d) adverse events (nature and number). The regular monthly research staff meetings will provide an opportunity for continual evaluation to gauge whether the various components of the study work well together as well as allowing collection and monitoring of data relating to the key parameters that have been identified in (a–d) above.

In order to meet the target sample size, it is planned that the recruitment coordinator will achieve a telephone screening percentage of 75%, and the assessors at each site will achieve a clinical assessment screening percentage of 50%; screening will continue until the target population is reached (12 participants per site [38]. As making a diagnosis of SPS is complex [40, 41, 43–45], an assessment algorithm (see Fig. 2) has been designed in order to ensure the appropriate participants are included in this study [42]. Part of the feasibility of this study relates to the ease of use of the assessment algorithm by the assessors, their willingness to use it and its influence on recruitment rates. Calculating the time it takes to recruit will facilitate planning for the full-scale RCT.

Participant adherence will be monitored by recording the number of physiotherapy assessment and treatment sessions attended. For completeness of data collection and improved statistical analysis, we seek to maximise study retention and adherence. In accordance with the Pedro Scale criteria [46], we plan for a retention rate of at least 85%. By keeping the intervention period relatively short to reduce the patient burden as well as by contacting participants to remind them of their treatment and assessment appointments, we anticipate this will be achievable.

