#### Secondary outcomes: shoulder-related symptoms and disability (WORC, SPADI), strength (hand-held dynamometer), pain (NRS/VRS), perceived change (GRCS)

As this is a pilot study, it is not fully powered to determine treatment effects, and any inferential statistics will be used cautiously. Nevertheless, the analysis of between-group changes in secondary outcomes at each of the follow-up time-points may offer insights into possible trends and guide the design of a future full-scale RCT [61]. Similarly, baseline between-group participant characteristics and any associated influence on outcomes may also be observed. All data will be analysed as per-protocol. Analyses of variance (ANOVA) with repeated measures will be undertaken to evaluate trends in between-group changes in secondary outcome scores, with post-hoc analyses using Tukey’s HSD test performed where significant between-group differences are observed. Continuous variables (SPADI, WORC, 11-point NRS, VRS, hand-held dynamometer and GRCS) will be summarised using means and standard deviations, or medians and interquartile range, while categorical variables (gender) will be summarised using frequencies and proportions (and 95% confidence intervals). Analysis will be undertaken using SPSS statistical packages (Version 24, SPSS Inc. Chicago, IL) with estimation of effect sizes and confidence intervals; significance set at *p* < 0.05.

All data will be de-identified with analyses performed by an independent analyst. Groups will be coded and intervention allocation undisclosed so that the analyst is blind to the exercise program being used in any of the groups. Hard data will be stored in a locked cabinet and all soft files held on a password-protected computer accessible only to the research team. The principle investigator will have access to the final datasets. Results will be made available to participants on request and will be published in a peer-reviewed journal.

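### Blocking is offered as the answer to public/private differences, but it balances arms within clinics only if blocks are formed per clinic, which the text leaves open

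*Protocol article*

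**What the plan says.** Recruitment is from "a physiotherapy outpatient clinic at a large public hospital and two private physiotherapy clinics" (Participants). The total is fixed there too: "a sample of 36 across the three groups (12 per group) has been chosen for this pilot study". The feasibility section adds a site target: "screening will continue until the target population is reached (12 participants per site".

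Under Procedures the reason for the allocation method is "Since there is a possibility of baseline differences in demographics between participants recruited from the public and private sectors", and the remedy is that "block randomisation will be used to ensure that participants from each of the clinics have an equal chance of receiving any of the interventions". The mechanism follows: "participants will be randomly allocated using an off-site randomiser and computer-generated allocation sequence to one of the three exercise groups". The article gives no block size, does not mention stratification, and does not say whether the randomiser holds one list or one per clinic.

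For the secondary outcomes, "Analyses of variance (ANOVA) with repeated measures will be undertaken to evaluate trends in between-group changes in secondary outcome scores". No clinic or sector term is named. The same section says that the influence of baseline characteristics on outcome may be looked at, without fixing an adjustment.

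**The concern.** The reason given does not match the problem named. The problem is that public and private patients may differ, so the arms could end up with different mixes of the two. An equal chance of each arm does not prevent that: simple 1:1:1 randomisation already gives it to every participant at every clinic. Blocking adds control over the numbers per arm within whatever list is blocked. A list for the whole trial equalises the arm totals and leaves the clinic-by-arm split to chance. A list per clinic balances the arms within clinic, which is what the sentence appears to want.

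Clinic carries more than demographics. By the article's own account, self-referral is possible only at the private clinics, and each site has its own treating and assessing physiotherapists. With 12 per arm, a lopsided clinic split can shift the between-group estimates that the article wants for planning the full-scale trial. An imprecise description of the allocation could also be carried into that trial.

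**Working it through.** The plan gives no figure of its own for within-clinic balance, so there is none to reproduce.

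**Inputs from the article.** 3 sites (1 public, 2 private); 36 participants; 3 arms of 12; 12 participants per site. These agree: 3 × 12 = 36.

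**Assumptions not in the article.** Exactly 12 are recruited at each site and, for the single-list reading, participants arrive in random order across sites.

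**Reading A: one trial-wide list.** Under random arrival, each clinic's participants are a random 12 of the 36 list positions, and the list holds 12 of each arm. The block size then drops out. Simulation with blocks of 3, 6, 9, 12 and 36 agreed to within about 0.02 on every measure below.

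For one clinic, P(a, b, c) = C(12,a) × C(12,b) × C(12,c) / C(36,12), with a + b + c = 12.

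- Exact 4/4/4: C(12,4)³ / C(36,12) = 495³ / 1,251,677,700 = 0.097.
- Gap of 4 or more between the largest and smallest arm (for example 6/4/2), summing the formula over all such splits: 0.283.
- At least one of the three clinics with such a gap, by enumerating all 3 × 3 tables with margins of 12: 0.551.
- All three clinics exactly 4/4/4: [12!/(4!)³]³ / [36!/(12!)³] = 34,650³ / 3.385 × 10¹⁵ = 0.012.

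**Reading B: one list per clinic.** With fixed blocks of 3, 6 or 12, every clinic is 4/4/4 in all runs, so the imbalance is zero. With a block size that does not divide 12, such as 9, exact balance is not guaranteed, but a gap of 4 or more never occurred.

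**What an imbalance does.** If the public site splits 6/4/2, the extreme arms are 6/12 and 2/12 public. The difference, 4/12 or one third, is the share of any public-private difference in the analysed outcome that passes into the unadjusted contrast between those two arms.

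**Check on the remedy.** Drawing blocks of 3 and 6 at random with equal probability and no constraint does not reliably fill 12. Count in units of 3 and let h(k) be the chance that a block ends exactly at k units. Then h(k) = ½h(k−1) + ½h(k−2), with h(0) = 1 and h(1) = 1/2. So h(2) = 3/4, h(3) = 5/8 and h(4) = 11/16 = 0.69. All three clinics finish on a block boundary with probability (11/16)³ = 0.32. The block sequence therefore has to be constrained to total 12.

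**The case against.** A reader might infer that the trial is unstratified. The article does not say so. The sentence refers to participants from each clinic, its stated motive is differences between sectors, and 12 per site with 12 per group fits 4/4/4 at every clinic. Blocking within clinic is a natural reading, and list structure and block size are details that a condensed article often leaves to the full protocol. This stands: the text is ambiguous and does not show a wrong design. What remains is that the reason given is wrong under either reading.

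The imbalance figures belong to the single-list reading with random arrival. If a clinic recruited in runs, small trial-wide blocks would largely balance it as well. This also stands.

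A reader might also infer that the analysis ignores clinic. The article names a model family without listing or excluding covariates, and an analysis plan that is not shown may add the term. The absence of a clinic term is therefore not an error in itself.

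Nor is clinic systematically confounded with contraction type. Unstratified 1:1:1 allocation is valid, and any imbalance arises by chance. Because between-group changes are analysed, constant clinic or tester offsets largely cancel within participant, leaving clinic differences in response. The primary outcome is feasibility, reported as percentages, and the article says that inferential statistics will be used cautiously. All of this limits the severity.

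**Conclusion.** The point holds as a minor one. The equal-chance rationale is mistaken, and the text does not establish that the named risk is controlled. The size depends on the reading: zero imbalance with per-clinic blocks that fill exactly at 12; with one trial-wide list, about a 28% chance of a gap of 4 or more at a given clinic and about 55% at one clinic or more. The single-list figures assume exactly 12 per site and random arrival order.

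The consequence is chance imbalance and lost precision in exploratory between-group estimates. If allocation is stratified and clinic affects the outcome, leaving clinic out of the model keeps its variance in the error term and makes standard errors too large, so the error is conservative.

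**What to change.** - **Allocation.** State that randomisation is stratified by clinic, with a separate permuted-block list for each clinic held by the off-site randomiser. Make each list's blocks total 12, for example a concealed random ordering of blocks of 3 and 6 constrained to that sum. Do not disclose block sizes to site staff: the treating physiotherapists know the allocations, and small known blocks would make later ones easier to guess.
- **Rationale.** Replace the equal-chance wording with balance of the arms within each clinic.
- **Analysis.** Include clinic as a fixed factor in the between-arm repeated-measures models, so that the analysis reflects the factor that the randomisation is meant to control.

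The cost is three lists instead of one and 3 − 1 = 2 degrees of freedom. If all 36 participants are analysed, the between-participant error falls from 36 − 3 = 33 to 31. If per-clinic lists are already in use, the allocation item is a change of wording only.

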### Outcome measures

#### Primary outcome: feasibility of a full-scale RCT

The primary outcome of this study is to determine feasibility for a full-scale RCT. This will involve an evaluation of (a) ease of recruitment (rate and number as well as suitability of the assessment algorithm), (b) adherence to both phases of the exercise intervention including home program compliance and logbook completion, (c) participant non-completion (drop out number and rate) and (d) adverse events (nature and number). The regular monthly research staff meetings will provide an opportunity for continual evaluation to gauge whether the various components of the study work well together as well as allowing collection and monitoring of data relating to the key parameters that have been identified in (a–d) above.

In order to meet the target sample size, it is planned that the recruitment coordinator will achieve a telephone screening percentage of 75%, and the assessors at each site will achieve a clinical assessment screening percentage of 50%; screening will continue until the target population is reached (12 participants per site [38]. As making a diagnosis of SPS is complex [40, 41, 43–45], an assessment algorithm (see Fig. 2) has been designed in order to ensure the appropriate participants are included in this study [42]. Part of the feasibility of this study relates to the ease of use of the assessment algorithm by the assessors, their willingness to use it and its influence on recruitment rates. Calculating the time it takes to recruit will facilitate planning for the full-scale RCT.

Participant adherence will be monitored by recording the number of physiotherapy assessment and treatment sessions attended. For completeness of data collection and improved statistical analysis, we seek to maximise study retention and adherence. In accordance with the Pedro Scale criteria [46], we plan for a retention rate of at least 85%. By keeping the intervention period relatively short to reduce the patient burden as well as by contacting participants to remind them of their treatment and assessment appointments, we anticipate this will be achievable.

Compliance with the exercise intervention will be monitored via therapist logbook sign off at each treatment session. In studies that have investigated exercise interventions in participants with SPS, adherence to intervention protocols has been reported as 80% and over [47, 48]. We consider this will be achievable in our study with the exercise check-review during week 9, specifically designed to ensure ongoing compliance.

As well as participants recording adverse events in their logbook, further questioning regarding this will be undertaken by the assessor at trial completion. As all groups in this study will undertake an exercise-based intervention only, serious adverse events are not anticipated. Increased short-term pain during and following performance of exercises has been reported in other exercise-based studies [47]. As all of our participants will undergo a structured semi-individualised exercise program, with progression governed by symptoms and stage of tendon pathology, we anticipate minimal reporting of these kinds of minor adverse events.

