### Physiotherapy intervention

The physiotherapy intervention will involve two treatment phases. In Phase 1, participants will attend on four consecutive weekly occasions for one-on-one treatment sessions with the physiotherapist. The intervention is exercise-based and aims to address (i) altered scapulo-humeral movement patterns, (ii) rotator cuff strengthening and (iii) upper quadrant flexibility/building posterior musculature (see Table 1). Participants will be taught the exercises at each visit with the intervention progressing in the following stages:

**Table 1 Tab1:** Physiotherapy intervention overview

Treatment		Aim	Exercise	Description
Session 1	Retrain scapular movement patterns.	Scapular stability/retraining: optimise the position of the scapular and humeral head during shoulder motion, restoring normal scapulo-humeral rhythm.	Scapular setting. Scapular shrugs.	Scapular setting in standing at 0° with scapular rotation/ tilt correction (based on individual deficits). Build scapular stability-progression to scapular shrugs.
Session 2	Improve rotator cuff strength.	Improve rotator cuff strength (in optimal scapulo-humeral movement pattern).	Shoulder external rotation strengthening in neutral.	External rotation in standing with elastic (isotonic) or rigid (isometric) resistance band. Shoulder adducted to side and elbow at 90°.
Session 3	Improve rotator cuff strength.	Improve rotator cuff strength (in optimal scapulo-humeral movement pattern).	Shoulder internal rotation strengthening in neutral.	Internal rotation in standing with elastic (isotonic) or rigid (isometric) resistance band. Shoulder adducted to side and elbow at 90°.
Session 4	Build posterior musculature and restore flexibility.	Improve posterior muscle strength.	Standing rows at 45° or 90°.	Bilateral standing rows progressing from 45° to 90° shoulder abduction with resistance band.
		Improve flexibility of upper quadrant soft tissues.	Anterior shoulder stretch. Active thoracic extension. Lateral neck stretches.	Bilateral anterior chest stretch using room corner/door jamb. Sternal lift in sitting with lumbar-thoracic dissociation. Neck stretches in stand/sit.

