**Fig. 3 Fig3:**
[figure not shown]
Rotator cuff strengthening exercises—between group variation, ER external rotation, IR internal rotation

Treatment 4 will address areas of relative flexibility including the thoracic spine and upper quadrant soft tissues as well as building posterior musculature. For the thoracic spine mobility exercises, retraining may be performed in varying positions, aimed at minimising compensatory strategies. Specific upper quadrant soft tissue flexibility exercises will include a bilateral anterior shoulder/chest stretch and lateral neck flexor stretches. Posterior muscle building will involve standing rows, taught and progressed at 45° and/or 90° determined by individual ability.

Throughout Phase 1, home exercises based on the treatment intervention will be given with exercise progression as per individual response to load, aiming to maximise training effects. These will be performed independently and daily, dose dependent on exercise type. Participants will be provided with an exercise manual. Figure 4 outlines the Phase 1 home exercise program for the isometric group with the programs for the concentric and eccentric groups available as supplementary material [Additional files 1 and 2].

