**Fig. 4 Fig4:**
[figure not shown]
Phase 1 home exercise program—isometric group

To standardise treatment as much as possible and since this study is primarily focussed on exercise intervention, manual therapy techniques will not be routinely used. Consistent with the usual clinical care of patients with this shoulder disorder, for individual participants who are unable to progress beyond an exercise stage without manual therapy to facilitate, this will be undertaken but kept to a minimum and recorded.

Phase 2 of the treatment intervention commences on completion of the 6-week follow-up assessment, when participants will be provided with an exercise sheet [Additional file 3] designed to progress them from 0° into range (and therefore no longer specific to one or more of the muscle contractions being evaluated in the trial). These exercises are based on the treatment intervention and home program. The patient will be instructed on how to perform the exercises that take them into a higher range of motion, focus on further strength gains and return to function. At week 9, they will attend a one-on-one check-review to ensure compliance with the exercise sheet.

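### Adverse events are part of the primary feasibility outcome, but the only questioning the plan schedules is at trial completion, after arm-specific loading has ended and beyond the reach of participants who withdraw

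*Protocol article*

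**What the plan says.** The Outcome measures section (Primary outcome) lists four feasibility parameters, the last being "d) adverse events (nature and number"). Three routes for capturing events are described.

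- **Logbook.** Participants record events in a logbook (Procedures; Primary outcome).
- **Treating physiotherapist.** Under Procedures, "All adverse events will be documented by the treating physiotherapist and the project coordinator informed". No timing is given, and no instruction to ask.
- **Assessor.** Under Primary outcome, "As well as participants recording adverse events in their logbook, further questioning regarding this will be undertaken by the assessor at trial completion". This is the only route described as questioning.

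The contact schedule is in the Physiotherapy intervention section. In Phase 1, "participants will attend on four consecutive weekly occasions for one-on-one treatment sessions with the physiotherapist". Group-specific strengthening is taught at sessions 2 and 3. Home exercises continue throughout Phase 1: "These will be performed independently and daily, dose dependent on exercise type". Phase 2 follows the 6-week assessment and no longer differs by contraction type. "At week 9, they will attend a one-on-one check-review to ensure compliance with the exercise sheet". The therapist signs off the logbook at each treatment session, with compliance as the stated purpose.

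On retention, "we plan for a retention rate of at least 85" per cent.

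**The concern.** The plan does more than leave the detail of event collection unstated. It names a time for questioning, and on its own schedule that time is a poor one. The harm it foresees is short-term pain during and after exercise, and the arms differ only in Phase 1. A question at the end of the trial comes well after that phase and after a second programme that all arms share. It is also tied to a point that participants who leave early do not reach, and some of them may leave because of symptoms.

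The logbook is a weak substitute, because logbook completion is one of the things the pilot sets out to test under component (b). If it is poorly kept, the event count suffers with it.

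At stake is one of the four parameters meant to inform the full-scale RCT. The protocol expects few minor events to be reported, and weak ascertainment could produce that result whatever the true rate.

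**Working it through.** The plan gives no figure for event ascertainment, so there is none to reproduce. The check uses the plan's own counts and dates.

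**1. Who can miss the questioning.** Inputs: 36 participants (Participants section) and retention of at least 85% (Primary outcome).
- Expected loss at exactly 85%: 36 × (1 − 0.85) = 5.4.
- Smallest whole number of completers that meets the target: 0.85 × 36 = 30.6, so 31.
- Largest loss that still meets the target: 36 − 31 = 5, or 5/36 = 13.9%.

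Five is an upper end under the target, not a forecast.

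**2. Whether that could matter.** The documents give no event risk, so a range is assumed. With risk p per participant, independent between participants, the chance that at least one of 5 drop-outs had an event is 1 − (1 − p)^5.

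| Assumed p | 1 − (1 − p)^5 | Expected number among 5 |
|---|---|---|
| 10% | 1 − 0.590 = 41% | 0.5 |
| 20% | 1 − 0.328 = 67% | 1.0 |
| 40% | 1 − 0.078 = 92% | 2.0 |

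This is the chance that there is something to find. It is not the chance that it is missed, because the logbook or the therapist may already have recorded it.

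**3. Delay between event and question.** Arm-specific loading starts at session 2 (about week 2 if session 1 is in week 1) and ends at week 6. If trial completion means week 12:
- longest delay: 12 − 2 = 10 weeks;
- shortest delay: 12 − 6 = 6 weeks.

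The article also has a 6-month postal review. If completion meant that point, the delay would be longer.

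**4. Therapist contact during arm-specific loading.** Four weekly sessions from week 1 cover weeks 1 to 4, and Phase 1 lasts 6 weeks (Abstract, Methods). So 6 − 4 = 2 weeks have no treatment session: 2/6 = 33% of Phase 1, or 2/5 = 40% of weeks 2 to 6. From the session in week 4 to the next named one-on-one session at week 9 is 9 − 4 = 5 weeks.

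**5. Contacts against stated questioning.**

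| Contact | Stated purpose | Event question stated? |
|---|---|---|
| Sessions 2, 3 and 4 | treatment; logbook sign-off for compliance | no |
| Week 6 | outcome assessment | no |
| Week 9 | check on compliance | no |
| Withdrawal | none described | no |
| Trial completion | assessor | yes |

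**The case against.** The strongest reply is that capture is wider than one question. The treating physiotherapist must document all events and the coordinator is informed. The logbook is seen and signed at each treatment session. Monthly staff meetings monitor all four feasibility parameters, adverse events included. Pain is rated before and after the group-specific contractions at sessions 2 and 3, and again at week 6, so early pain response is measured even though it is not labelled as an adverse event. Visit-level prompts and form fields are also details that an article may leave to the full protocol.

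Much of this stands, and it limits the point. A reader might infer three stronger things that the documents do not support.

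- **That drop-outs are never asked about events.** The article is silent on withdrawal contact; it does not rule it out. An event before withdrawal may already be in the therapist's record.
- **That weeks 5 and 6 are reached only by a self-kept logbook.** For completers, the final questioning has no stated recall limit and so covers those weeks. Completers are also seen at weeks 6 and 9. Someone, not identified, instructs them when Phase 2 begins, so the 5-week gap lies between named sessions and is not a gap in all contact.
- **That the reported event rate will be too low by some stated amount, with blank logbooks counted as event-free.** No such counting rule appears, and any figure would need invented event rates plus zero capture by the other routes.

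The reply does not remove the remaining problem. None of these routes is stated to involve asking about events before the end, and the one scheduled question is placed late.

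A further fair point concerns blinding. If the assessor asked about exercise-related events at week 6, the answer could reveal the contraction type before the week 12 measurements. The fix has to avoid that.

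**Conclusion.** The concern holds in a limited form. For a component of the primary outcome, the single scheduled question comes at trial completion ("further questioning regarding this will be undertaken by the assessor at trial completion"), and earlier capture depends on self-recording and unprompted clinician documentation. Up to 5 of 36 participants may miss the question with the retention target met. Completers are asked about arm-specific events 6 to 10 weeks afterwards. Under-counting, and difficulty in placing events in Phase 1 or Phase 2, are plausible, but their size cannot be derived from the documents.

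This rests on session 1 falling in week 1, on trial completion meaning week 12, and on the article stating the questioning schedule in full. If the full protocol already prompts for events at each visit and at withdrawal, the point reduces to saying so in the article. It is a worthwhile, cheap improvement and not a flaw that undermines the pilot.

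**What to change.** **Procedures and Outcome measures (Primary outcome).** Keep the end-of-trial questioning. Add one fixed, open adverse-event question, with the onset date recorded so that each event can be placed in Phase 1 or Phase 2. It would be asked:
- by the treating physiotherapist at sessions 2, 3 and 4 and at the week 9 review;
- by the coordinator, not the blinded assessor, around week 6;
- by the coordinator, by telephone, when a participant withdraws.

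**Data management and analysis (Primary outcome).** The current list of feasibility data does not name adverse events. Add the number of participants with at least one event and the number of events, by arm and phase, for all randomised participants who started treatment. Show those neither questioned nor returning a logbook as not ascertained, separately from those with no event.

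**Cost.** One short question at contacts that already exist, a short coordinator contact around week 6, one call per withdrawal (up to about 5 if the retention target is met), and a few sentences of protocol text. The reported event rate may look less favourable. No visit is added and no treatment rule changes.
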